### 2.8 Clinical information collection

All participants will complete a face-to-face paper questionnaire and undergo a comprehensive physical examination. The questionnaire and examination will cover general characteristics, menstrual history, menopausal age, pregnancy and childbirth history, education and income levels, smoking and drinking habits, medical and medication history, fall frequency, dietary habits, and TCM syndrome classification. Detailed information on fractures, including frequency, causes, locations, and treatments, will also be collected.

Based on relevant standards and guidelines, a preliminary TCM information collection form for PMOP-KOA participants was developed. Through multiple clinical pilot investigations and expert consultations, the questionnaire was continuously revised and refined, leading to the final information collection form and participant screening form. Additionally, the following scales will be used to assess physical activity levels and quality of life: International Physical Activity Questionnaire (IPAQ) (18), International Osteoporosis Foundation (IOF) 1-Minute Osteoporosis Risk Assessment Test (19), EuroQol 5-Dimension (EQ-5D) Instrument (20). Both the IPAQ and EQ-5D have undergone cultural adaptation and validation in Chinese populations in previous studies. Reliability analysis in similar cohorts reported Cronbach’s α values greater than 0.80, indicating good internal consistency. For this study, only validated Chinese versions of the IPAQ and EQ-5D will be used to ensure measurement accuracy and cultural relevance.

### 2.9 Follow-up study

A subsequent follow-up study will be conducted annually until July 2025. Participants who miss two or more consecutive scheduled assessments will be considered lost to follow-up. To minimize dropout, the study team will implement strategies such as regular reminder calls or messages, flexible scheduling of follow-up visits, and providing modest incentives. For handling missing data due to loss to follow-up, multiple imputation techniques will be used under the assumption that data are missing at random. Sensitivity analyses will be conducted to evaluate the robustness of results to different missing data mechanisms.

### 2.10 Primary outcomes

This study will be conducted in two phases. In the cross-sectional phase, the primary outcomes will include BMD and participants’ clinical information, which will be used for TCM classification and subsequent differential gene expression analysis. During the follow-up period, the incidence of osteoporotic fractures will be the most critical outcome. While self-reported data and interviews will provide valuable information on newly occurring fractures, all reported fracture cases will be immediately reassessed using DEXA to verify bone loss and confirm fracture events. Participants who experience fractures will be asked to provide detailed information, including the time and cause of the fracture, the affected site, and post-fracture treatment received. In cases of uncertainty, medical records and imaging reports will be reviewed to ensure accuracy.

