### 2.4 Inclusion and exclusion criteria

The inclusion criteria for this study are as follows: (1) Participants must have resided locally for more than 10 years; (2) Participants must meet the diagnostic criteria for KOA, with a KL grade of II or higher (unilateral or bilateral), and simultaneously fulfill the diagnostic criteria outlined in the Guidelines for the Diagnosis and Treatment of Primary Osteoporosis for comorbid osteoporosis; (3) Participants must be postmenopausal women aged 50–65 years (50 ≤ age < 65); (4) Participants must not have taken estrogen or medications affecting bone metabolism (e.g., glucocorticoids, antiepileptic drugs, aluminum-containing antacids, proton pump inhibitors, chemotherapy drugs, anticoagulants, or thiazolidinediones) within the past month; (5) Participants must voluntarily enroll in the study, sign an informed consent form, and ensure that the consent process fully adheres to ethical principles.

The exclusion criteria are as follows: (1) Participants with physical disabilities that severely limit mobility or the ability to comply with study procedures, as assessed by clinical investigators; (2) Participants with other autoimmune diseases; (3) Participants with serious heart, liver, or kidney comorbidities; (4) Participants who are pregnant or lactating; (5) Participants who have received immunosuppressive therapy within the last 3 months; (6) Participants who are unwilling or unable to complete follow-up.

To minimize recall bias in fracture reporting, all self-reported fracture events must be confirmed through radiographic evidence (X-ray or CT report); cases without objective imaging confirmation will be excluded from fracture-related analysis.

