### 2.5 Sample size

Through multiple clinical pilot investigations and expert consultations, a standardized participant information collection form has been developed and refined. Additionally, based on a comprehensive review of prior literature and expert discussions, this study has preliminarily identified the characteristic clinical symptoms and physical signs of PMOP-KOA. To estimate the required sample size, the Kendall method was initially applied, multiplying the number of variables by five, yielding a minimum sample size of 150 participants (15). To further enhance methodological rigor, a supplementary power analysis was conducted. Assuming a medium effect size (Cohen’s d = 0.5), a significance level (α) of 0.05, and a power (1–β) of 0.80, the required sample size for detecting group differences was calculated to be approximately 128 participants using standard formulas. Allowing for a 15% attrition rate due to potential loss to follow-up or incomplete data, the final target sample size was set at 150 participants. This dual approach ensures both practical feasibility and statistical robustness.

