### 2.6 Bone density assessment

A HOLOGIC Wi dual-energy X-ray absorptiometry (DEXA) scanner (United States) will be utilized to measure bone density at the lumbar spine and bilateral hips, recording the T-score and Z-score at each site. The instrument’s precision will be maintained at 1%, ensuring that the error in repeated measurements remains below 1%. Daily calibration and maintenance will be conducted by trained professionals to ensure measurement accuracy and optimal device performance.

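### Sections 2.4 and 2.10 confirm osteoporotic fractures by conflicting rules, and the DEXA scan named in 2.10 cannot show that a fracture occurred

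*Protocol article*

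**What the plan says.** Section 2.10 of the protocol article ranks the follow-up outcomes: "the incidence of osteoporotic fractures will be the most critical outcome". For new fractures learned from self-report and interview, it then states that "all reported fracture cases will be immediately reassessed using DEXA to verify bone loss and confirm fracture events". Imaging comes second: "In cases of uncertainty, medical records and imaging reports will be reviewed to ensure accuracy".

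Section 2.4, after the eligibility criteria, sets a different requirement: "all self-reported fracture events must be confirmed through radiographic evidence (X-ray or CT report"). It adds that "cases without objective imaging confirmation will be excluded from fracture-related analysis".

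Section 2.6 describes the DEXA examination. Its task is to "measure bone density at the lumbar spine and bilateral hips, recording the T-score and Z-score at each site". It mentions no fracture imaging and no other skeletal site.

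Sections 2.3 and 2.4 together admit only women who already meet the osteoporosis criterion, a T-score of −2.5 or below.

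**The concern.** An X-ray or CT report cannot be compulsory for every reported fracture and also be consulted only when a case is in doubt. Two teams following the two sections could count different events from the same reports.

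The DEXA step adds a second problem. A density scan answers a different question from whether a bone broke. If section 2.10 is followed as written, false reports can be accepted as events in the outcome that the protocol treats as most critical.

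The handling of unconfirmed reports is also not fixed. Excluding a case from the fracture analysis may mean that the event is not counted, or that the woman leaves the denominator. With a target of 150 women, fractures are likely to be few, so a small number of reclassified reports can change the incidence noticeably. If the rule is settled only after the reports are in, the data can influence the choice.

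**Working it through.** **1. The plan's own figures.** Section 2.5 gives a sample size but no fracture rate or event count. Its inputs are d = 0.5, α = 0.05 and power 0.80; section 2.11 makes tests two-sided.

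- Normal approximation: n per group = 2(z₀.₉₇₅ + z₀.₈₀)²/d² = 2(1.960 + 0.842)²/0.25 ≈ 62.8, so 63 per group and 126 in total.
- Two-sample t-test: 63.77, so 64 per group and 128 in total, as stated.
- 15% attrition: 128/0.85 = 150.6, so 151 against the stated 150.

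The sample size reproduces. It concerns a standardised mean difference, so it does not bear on how many fractures are counted.

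**2. The two rules side by side.**

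| | Section 2.4 | Section 2.10 |
|---|---|---|
| Reports covered | Every self-reported fracture | Every reported fracture |
| Routine confirmation | X-ray or CT report | DEXA |
| Role of imaging reports | Required for all | Reviewed if uncertain |
| Unconfirmed report | Excluded from fracture analysis | Not stated |

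The second and third rows conflict. No sentence says which section prevails or that both conditions must be met.

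**3. What the DEXA scan can show.** By section 2.6 the output is a T-score and a Z-score at the lumbar spine and both hips. A fracture at any other site is outside the scan. At the scanned sites, the output is a density value and not evidence of a break. Since osteoporosis is an entry condition, low density is expected in nearly every woman who reports a fracture, whether the report is true or false.

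**4. Illustration of size.** The documents give none of these inputs except N, so the rest are assumptions shown as ranges:

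- N = 150 (section 2.5), all followed, at most one report per woman.
- p = 4% to 10% of women report a fracture.
- s = 60% to 100% of reports have an X-ray or CT report.
- DEXA rejects no report.

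Reports: R = N × p. Confirmed by imaging: C = s × R.

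- Section 2.10 rule: R/N.
- Section 2.4 rule, woman kept as a non-event: C/N.
- Section 2.4 rule, woman removed: C/(N − (R − C)).

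| p | s | R | C (expected) | 2.10 rule | 2.4, kept | 2.4, removed |
|---|---|---|---|---|---|---|
| 4% | 100% | 6 | 6 | 4.0% | 4.0% | 4.0% |
| 4% | 80% | 6 | 4.8 | 4.0% | 3.20% | 3.23% |
| 4% | 60% | 6 | 3.6 | 4.0% | 2.40% | 3.6/147.6 = 2.44% |
| 10% | 100% | 15 | 15 | 10.0% | 10.0% | 10.0% |
| 10% | 80% | 15 | 12 | 10.0% | 8.00% | 8.16% |
| 10% | 60% | 15 | 9 | 10.0% | 6.00% | 9/144 = 6.25% |

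With women kept, the relative gap between the rules is 1 − s whatever the value of p: zero at full documentation and 40% at s = 60%. The two readings of the exclusion differ little: 2.40% against 2.44%, and 6.00% against 6.25%.

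**The case against.** The best defence is that the sections can be read together: section 2.4 sets a compulsory minimum, and section 2.10 adds a scan whose first stated purpose is to check bone loss. The text does not say this, and reserving imaging review for uncertain cases contradicts it. A second defence is that section 2.4 concerns fracture history, since it sits under eligibility and speaks of recall bias. Its wording covers all self-reported fracture events. If it did cover history only, new fractures would be left with DEXA as the routine confirmation. A third is that a fuller document may settle the matter. The point is not missing detail, however: the article states two rules that cannot both be followed.

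Some stronger readings are tempting but not supported:

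- *Three incompatible rules.* The two steps in section 2.10 form one procedure, so there are two rules.
- *The exclusion removes women and biases incidence downward.* Section 2.4 does not say that women leave the risk set. If they did, incidence would be slightly higher than with those women kept as non-events, as the table shows. Whether counting only confirmed events is too low depends on how many unconfirmed reports are true, which is unknown.
- *Only women who report a fracture are re-scanned, so their bone loss cannot be compared with that of others.* Section 2.9 provides annual follow-up without listing its content, and a condensed article may omit it.
- *Every hazard ratio is affected.* Section 2.11 names Cox models only as an example.

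**Conclusion.** The point holds as a conflict in the definition of the leading follow-up outcome. Sections 2.4 and 2.10 give two unreconciled confirmation rules. The DEXA examination as described cannot establish that a fracture occurred, least of all in women who all have osteoporosis at entry. The meaning of the exclusion in section 2.4 is also open.

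The textual conflict is certain; its numerical effect is not. The documents give no fracture rate and no share of reports with images. Under the assumed ranges, the relative difference in incidence runs from none to about 40%, with the upper end at 60% documentation and no report rejected by DEXA. A reader might take a particular shift as a prediction for this study, but the documents support none. This needs correcting before fractures are analysed.

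**What to change.** Reconcile sections 2.4 and 2.10 into one event definition, stated once and cross-referenced:

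- An incident fracture counts when an X-ray or CT report shows it. This applies to every report, not only to uncertain ones.
- The cause, which section 2.10 already collects, is used to classify the fracture as osteoporotic. Without this step, any fracture seen on imaging would count.
- DEXA is removed as confirmation of the event. This concerns only its role in counting fractures.
- Women with unconfirmed reports stay in the risk set. They count as non-events in the primary analysis and as events in a sensitivity analysis. This replaces the exclusion sentence in section 2.4.

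The cost is a change of wording in two sections and one extra sensitivity analysis. The downside is that some true but undocumented fractures go uncounted in the primary analysis; the sensitivity analysis shows how much that could matter.

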### 2.11 Data management and statistical analysis

Data entry and logical verification were performed by two independent personnel using an electronic management system (National Copyright Registration Number: 2023SR0693141) to handle missing and abnormal values, ensuring data accuracy. Quality control measures were established in accordance with the requirements of clinical epidemiological cross-sectional studies and the specific characteristics of TCM research (21, 22). For standardization, all knee X-ray imaging and BMD assessments for participants from all community sub-centers were conducted at Beijing Electric Power Hospital. All recorded data must be preserved as original records and must not be altered arbitrarily.

Statistical analysis was performed using R 4.3.1. Continuous variables are presented as mean ± standard deviation ($\bar{\text{x}}$ ± s), while categorical variables are reported as percentages. Fisher’s exact test or Chi-square test was used for between-group comparisons. Variance estimation was performed using Taylor series linearization and replication methods. A two-sided *P*-value < 0.05 was considered statistically significant.

To control for potential confounding variables—such as body mass index (BMI), physical activity, dietary habits, and history of estrogen treatment multivariable regression models (e.g., logistic regression or Cox proportional hazards models for time-to-event data) will be employed. In addition, propensity score matching (PSM) or inverse probability of treatment weighting may be used where appropriate to balance covariates among comparison groups and enhance causal inference validity.

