This prospective study will investigate conventional risk factors and relevant symptoms as reported in traditional Chinese medicine in populations with a high risk of PMOP (11, 12). Based on the findings of this preliminary research, we will then conduct a further cross-sectional survey and a prospective follow-up study in the Beijing community. This prospective study aims to investigate the prevalence of PMOP and KOA, explore associated risk factors, and provide evidence-based recommendations for their prevention and management. Additionally, the study will conduct transcriptomic analyses on samples from different subtypes of PMOP-KOA patients to identify differentially expressed genes (DEGs) with high specificity and sensitivity. These DEGs will serve as potential biomarkers for PMOP-KOA subtyping, offering valuable molecular insights into disease classification and paving the way for personalized treatment strategies. This research on “Beijing Community Postmenopausal Osteoporosis and Knee Osteoarthritis Screening: a cross-sectional and prospective Study (BEYOND)” will provide reliable data for the prevention of PMOP-KOA among community-dwelling residents in Beijing area.

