**Kellgren & Lawrence (KL) grading**	
No changes (normal)	0
Joint space appears normal (doubtful osteoarthritis)	I
Possible joint space narrowing (mild osteoarthritis)	II
Definite joint space narrowing with sclerosis (moderate osteoarthritis)	III
Severe joint space narrowing with significant sclerosis and bone deformities (severe osteoarthritis)	IV

Traditional Chinese medicine syndromes represent specific stages in KOA or PMOP progression, influenced by both internal and external factors. TCM-based treatment considers an individual’s constitution, environmental conditions, and seasonal changes, following the principle of “treatment based on syndrome differentiation.” This approach is fundamental in TCM, involving the identification of syndromes through symptom analysis and physical examination methods such as inspection, auscultation, olfaction, and palpation. By classifying patients based on syndrome differentiation, TCM provides a framework for stratifying individuals and selecting appropriate treatments tailored to distinct clinical presentations.

According to the Guidelines for the Diagnosis and Treatment of Osteoarthritis (2018 edition) and the Guidelines for the Diagnosis and Treatment of Primary Osteoporosis (2022 edition) issued by the China Association of Chinese Medicine, the primary TCM syndromes commonly observed in patients with KOA and PMOP include yang deficiency, yin deficiency, and combined yin-yang deficiency. In this study, syndrome classification will be conducted by two independent TCM practitioners with senior titles based on a standardized TCM four-diagnostic information collection form (inspection, listening/smelling, inquiry, palpation). In cases of disagreement, a third senior practitioner will be consulted for arbitration. Inter-rater reliability will be assessed using Cohen’s kappa coefficient to ensure diagnostic consistency. Participants will then be classified accordingly, and peripheral blood samples will be collected for high-throughput sequencing analysis.

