### 2.7 Biological sample collection

Blood samples will be collected from participants categorized by the three TCM syndrome classifications using PAXgene™ Blood RNA Tubes (16), with 2.5 mL of venous blood obtained per individual. Immediately after collection, samples will be stored at 4°C and subsequently transferred to a −80°C freezer on the same day following a stepwise freezing protocol. To minimize potential batch effects, all collected samples will be randomly assigned to RNA extraction and sequencing batches. Furthermore, RNA quality will be assessed using the RNA Integrity Number (RIN), and only samples with RIN ≥ 7 will be included in downstream analyses. All samples will be transported to the BGI Biological Sample Testing Center via dry ice cold chain logistics for subsequent RNA-seq high-throughput sequencing (17).

The same batch of blood samples used for RNA-seq will also be used for RT-qPCR validation. RNA (1 μg) will be used as a template for reverse transcription to synthesize complementary DNA (cDNA) (RK20403; ABclonal, Woburn, MA, United States). Target gene sequences will be obtained from the GenBank database, and primers will be designed using PrimerExpress Software v2.0. GAPDH will be selected as the internal reference gene, and its stability across different experimental conditions will be verified using geNorm and NormFinder algorithms. Experimental results will be analyzed using the relative quantification method, with 2^–ΔΔCt^ as the indicator to represent the relative gene expression levels.

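### RT-qPCR validation on the RNA-seq discovery samples confirms the measurement only and cannot support biomarkers of high sensitivity and specificity

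*Protocol article*

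**What the plan says.** Section 2.7 sends whole-blood RNA for "subsequent RNA-seq high-throughput sequencing" and then states: "The same batch of blood samples used for RNA-seq will also be used for RT-qPCR validation". No other participants or samples are set aside for validation anywhere in the article.

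The groups are the three syndromes named in section 2.3: "yang deficiency, yin deficiency, and combined yin-yang deficiency". The Introduction sets the aim, which is to "identify differentially expressed genes (DEGs) with high specificity and sensitivity", and adds: "These DEGs will serve as potential biomarkers for PMOP-KOA subtyping".

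Section 2.11 names tests for categorical data ("Fisher’s exact test or Chi-square test was used for between-group comparisons") and gives one threshold: "A two-sided *P*-value < 0.05 was considered statistically significant". It does not mention gene expression. No section gives a gene-level test, a threshold for declaring a gene, or a rule for multiple testing. The sample size in section 2.5 uses "a significance level (α) of 0.05, and a power (1–β) of 0.80".

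**The concern.** A gene can differ between syndrome groups because the syndromes differ biologically, or because of who happened to fall into each group. Measuring the same RNA with a second assay keeps the same women in the same groups, so a difference due to chance sampling of people is largely carried over. Agreement between RNA-seq and RT-qPCR then shows that the measurement is sound. It says little about whether the difference would be seen in other women, which is what a subtyping biomarker needs.

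The same applies to sensitivity and specificity. If they are computed in the women whose data selected the genes, they are optimistic, and re-assay of those women cannot reveal it. At stake is the biomarker conclusion in the Introduction and the Discussion. The fracture outcome in section 2.10 is not affected.

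**Working it through.** **1. The plan's own figures (section 2.5).** Inputs: d = 0.5, two-sided alpha 0.05, power 0.80, attrition 15%.

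- Normal approximation: n per group = 2 × (1.960 + 0.842)² / 0.5² = 62.8, so 63 per group and 126 in total. The exact t-test gives 63.8, so 64 per group and 128 in total. The stated 128 is reproduced.
- Attrition: 128 / 0.85 = 150.6, or 128 × 1.15 = 147.2. The stated 150 is reproduced within rounding.

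This calculation serves one two-group comparison at alpha 0.05. The article gives no error rate for the gene analysis, so there is no figure of that kind to reproduce.

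**2. Re-confirmation of chance genes.** None of the following inputs is in the document: 15,000 genes, no true difference in any of them, 50 women per group, one two-group contrast, and selection at unadjusted P < 0.05. Each measurement is a woman's true level (variance 1) plus assay noise (variance 1/r − 1), so that two assays of the same sample correlate at r. A gene counts as confirmed if the re-assay gives P < 0.05 in the same direction. There were ten simulated datasets per row.

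| r | Mean genes at P < 0.05 | Confirmed, same samples | Confirmed, new participants |
|---|---|---|---|
| 0.70 | 749.9 | 33.2% | 2.3% |
| 0.80 | 743.6 | 44.1% | 2.5% |
| 0.90 | 742.7 | 59.4% | 2.4% |
| 0.95 | 732.9 | 70.3% | 2.7% |

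A closed form agrees. The two test statistics are roughly bivariate normal with correlation r, so the confirmed share is 2 × P(Z₁ < −1.96, Z₂ < −1.96) / 0.05, which gives 33%, 44%, 59% and 71%. In new participants the expected share is 0.05 / 2 = 2.5%. The excess is therefore about 33 / 2.5 = 13-fold to 70 / 2.5 = 28-fold.

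**3. Optimism in accuracy.** Under the same assumptions, the most extreme of 15,000 null genes has |z| of about 3.99 (upper tail 1/30,000). The apparent standardised difference is 3.99 × √(2/50) = 0.80, and the apparent AUC is Φ(0.80/√2) = 0.71, where the true value is 0.50.

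**4. If the general threshold were applied gene by gene.** Expected false genes = number of genes × 0.05.

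- 10,000 genes: 500 per contrast, and 1,500 over three pairwise contrasts.
- 20,000 genes: 1,000 per contrast, and 3,000 over three.

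With Benjamini-Hochberg at 5% and no true differences, any false gene would be declared in about 5% of analyses of a contrast. In the simulation this happened in 0 or 1 of 10 datasets per row.

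**The case against.** A reader might infer that the plan judges genes at raw P < 0.05 with no false-discovery control, and that chance genes will therefore be declared and then confirmed. The document does not support that. The threshold in section 2.11 closes a paragraph on descriptive statistics, categorical tests and variance estimation, and is never tied to gene expression. It does not rule out adjusted P-values for genes. The article gives no sequencing analysis at all, and a condensed article may leave that to a full protocol or analysis plan. Silence on multiplicity is therefore not evidence that there is none. This objection stands, so the false-gene counts in step 4 are conditional.

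A second objection is that the sizes in step 2 rest on assumptions. That also stands. It would be wrong to say that qPCR would confirm most chance genes: at correlations of 0.70 to 0.80 it confirms fewer than half. Only the range can be given.

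A third is that the article claims little. It speaks of potential biomarkers, describes no accuracy evaluation and does not call the validation independent. This softens the point but does not remove it. The article calls the step validation, sets high specificity and sensitivity as the aim, and offers no other evidence that the genes generalise. An analysis plan that is not shown could supply a multiplicity rule, but the article has already fixed which samples serve for validation. Nor would false-discovery control alone remove the optimism in accuracy measured in the selecting samples.

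**Conclusion.** The point holds for the validation step. RT-qPCR on the discovery samples is a check of measurement. It cannot support the aim of genes with high sensitivity and specificity as subtyping biomarkers. This follows from section 2.7 as written and needs no assumption.

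Its size can only be illustrated. With no true differences, unadjusted selection and 50 women per group, about 33% to 70% of chance genes would be re-confirmed for assay correlations of 0.70 to 0.95, against about 2.5% in new participants.

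On the threshold, the supportable statement is narrower. The only rule given is a general P < 0.05, and the article should say how genes are declared. Applied gene by gene to 10,000 to 20,000 null genes, that rule would give about 500 to 1,000 false genes per contrast, but the article does not say that it will be so applied.

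**What to change.** - Section 2.7: call RT-qPCR on the RNA-seq samples *technical confirmation* rather than validation.
- Introduction and analysis section: report any sensitivity and specificity of the selected genes from cross-validation that repeats the gene selection within each fold, and not from the samples that chose them.
- Section 2.11: limit two-sided P < 0.05 to single clinical outcomes, and declare differentially expressed genes at a Benjamini-Hochberg false discovery rate below 0.05 within each syndrome contrast.

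The cost is some extra analysis work, fewer declared genes and less favourable accuracy figures. No new participants or samples are needed.

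A reserved hold-out set is not required. With 150 women split equally over three syndromes (an assumption), reserving one third leaves 50 / 3, or about 17 per group. Power at the plan's own d = 0.5 would then be only about 29% per gene at P < 0.05, so true differences would often fail.
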